## 6.7 Adjustment using covariates

If a significant difference is seen for the demographic and other baseline characteristics and the difference is determined to be medically significant, an analysis of the primary endpoint will be performed using the Cox proportional hazard model with this factor as a covariate, and an adjusted hazard ratio will be calculated.

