## 6.5 Significance level and confidence coefficient

Because the evaluation of superiority with respect to the primary endpoint will be based on repeated tests, including the interim analysis, an increase in type I errors resulting from multiplicity will occur. Therefore, significance levels (two sided) will be selected using the Haybittle-Peto ad-hoc method.

Interim analysis significance level: 0.0027 (corresponds to  $z = 3$ )

Significance level for final analysis: 0.05

The significance level of the tests used in the other efficacy and safety evaluations will be a two-sided level of 5%. A two-sided significance level of roughly 5% will also be used for other evaluations, although an explicit significance level will not be established.

The confidence coefficient used for the estimates will be 95% (two sided).

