## 8. DESCRIPTION OF ANALYSIS SETS

### 8.1 Demographic and other baseline characteristics

Descriptive statistics (no. of subjects, mean, standard deviation, minimum, median, maximum) will be calculated by treatment group for the following variables, and the differences between the groups will be examined using the Wilcoxon test: age, height, weight, BMI, duration of morbidity, blood pressure (systolic and diastolic) on first day of observations, and laboratory values (WBC, RBC, hemoglobin, hematocrit, platelet count, AST, ALT, TC, TG, HDL-C, creatinine, fasting blood glucose, HbA1c).

Frequency distributions for each group will be determined for the variables shown in Table 8.1, and the differences between the groups will be examined using the chi-square or Wilcoxon test.

Table 8.1. Demographic and other baseline characteristics

| Variable                              | Category                                      |
|---------------------------------------|-----------------------------------------------|
| Sex                                   | Male, Female                                  |
| Age                                   | up to 49, 50 to 59, 60 to 69, 70 and older    |
|                                       | up to 64, 65 and older                        |
| Duration of morbidity (days)          | up to 28, 29 to 56, 57 to 112, 113 and longer |
| BMI                                   | < 25, ≥ 25                                    |
| Past history and concomitant diseases |                                               |
| Coronary artery disease               | No, Yes                                       |
| Peripheral artery disease             | No, Yes                                       |
| hypertension                          | No, Yes                                       |
| Diabetes mellitus                     | No, Yes                                       |
| Dyslipidemia                          | No, Yes                                       |

|                                                            |                                               |
|------------------------------------------------------------|-----------------------------------------------|
| Chronic renal disease                                      | No, Yes                                       |
| History of symptomatic ischemic stroke                     | No, Yes                                       |

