## **9. EFFICACY EVALUATION**

### **9.1 Primary endpoint**

The first recurrence of ischemic stroke between the first and last observation days (during the observation period) will be included in the analysis.

Subjects discontinued for reasons other than occurrence of the primary endpoint and subjects who continue to study completion will be treated as censored subjects. The censor date will be considered the observation completion date.

- 1) A between-groups comparison for the period from the observation start date to the date of ischemic stroke recurrence will be performed using the log-rank test, and the superiority of the combination therapy group versus the monotherapy group will be examined.
- 2) Survival coefficients for the period from the observation start date to the date of ischemic stroke recurrence will be estimated for each treatment group using the Kaplan-Meier method and plotted.
- 3) The hazard ratio for ischemic stroke recurrence in the combination therapy group versus the monotherapy group and its 95% confidence interval will be determined using a Cox proportional hazard model.
- 4) An adjusted hazard ratio will be calculated using a Cox proportional hazard model that includes as covariates age (each 1 year), sex, ischemic stroke clinical subtype (atheromic, lacunar, other, unknown), mRS (ordered categorical data).
- 5) The annual incidence in each group will be calculated using the person-year and Kaplan-Meier methods. The 95% confidence interval of the incidence will be calculated using the approximate Poisson method and the Greenwood method. One year will be considered 365.25 days for the calculations.

- 6) A subgroup analysis will be performed for each variable shown in Table 6.8 using a Cox proportional hazard model that includes a comparison group and predictive factors. The hazard ratio for the combination therapy group versus the monotherapy group will be calculated for each stratification category based on the predictive factors. Uniformity will be examined for the stratification categories based on the interaction between the comparison group and predictive factors.
- 7) Frequency distributions for each treatment group will be determined for the findings regarding the clinical subtype of ischemic stroke (lacunar, atherothrombotic, other, unknown) and responsible lesion (supratentorial, infratentorial, both, unknown) at the time of ischemic stroke onset.

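### SAP 6.7 lets baseline significance tests plus an unassigned medical judgement choose covariates for a second adjusted hazard ratio

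*Supplement*

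**What the plan says.** **The rule.** SAP 6.7 sets two conditions: "If a significant difference is seen for the demographic and other baseline characteristics and the difference is determined to be medically significant". If both hold, the primary endpoint is analysed in a Cox model "with this factor as a covariate, and an adjusted hazard ratio will be calculated". The section names no decider, criterion or timing, and does not require blinding to outcome.

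**The tests that feed it.** SAP 8.1 compares the groups on continuous variables ("the differences between the groups will be examined using the Wilcoxon test: age, height, weight, BMI, duration of morbidity, blood pressure (systolic and diastolic") and on "laboratory values (WBC, RBC, hemoglobin, hematocrit, platelet count, AST, ALT, TC, TG, HDL-C, creatinine, fasting blood glucose, HbA1c". For categorical variables it says: "Frequency distributions for each group will be determined for the variables shown in Table 8.1, and the differences between the groups will be examined". SAP 6.5 sets the threshold for such tests only loosely: "A two-sided significance level of roughly 5% will also be used for other evaluations, although an explicit significance level will not be established".

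**The adjusted model already fixed.** SAP 9.1 item 4 states: "An adjusted hazard ratio will be calculated using a Cox proportional hazard model that includes as covariates age (each 1 year), sex", followed by clinical subtype and mRS. Protocol v1.3 section 11.3 names the same four factors. It also provides for between-group tests of baseline data, but does not tie them to the choice of covariates.

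**The primary test.** SAP 9.1 item 1 is an unadjusted log-rank comparison.

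**The concern.** Allocation is randomised in blocks by centre (protocol 4.2). If that is done soundly, a significant baseline difference is a chance finding. It says nothing about whether the factor predicts recurrent ischaemic stroke, which is what makes a covariate worth including. A rule that selects on imbalance can bring in a weak factor that happens to differ and pass over a strong one that happens to be balanced.

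What is at stake is the supportive adjusted estimate. The plan could end with two or more adjusted hazard ratios and no statement of how they rank. It does not say whether a flagged factor enters alone or on top of the four fixed ones, or whether several flagged factors enter together or one at a time. Since neither the decider nor the timing is given, a choice made with outcome data in hand is not excluded.

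The second estimate could also rest on fewer patients. Under protocol 6.3.1 the imaging behind microbleeds and both stenosis variables is optional, and HbA1c is measured only in patients with diabetes. SAP 6.4 imputes nothing. A Cox model adjusted for one of these would drop patients who lack the value.

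**Working it through.** The documents give no figure for the number of baseline tests or the chance that 6.7 is triggered, so there is none to reproduce on this point. The sample size shows which analysis carries the trial's claim, so I checked that first.

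**1. Sample size (protocol 11.1, SAP 4).** Inputs: 4% and 2.8% per year (hazard ratio 0.70), 2.5 years' accrual, 3.5 years' maximum observation, two-sided 5%, 80% power.
- Events by Schoenfeld's formula: 4 × (1.960 + 0.842)² / (ln 0.70)² ≈ 247.
- Event probability with uniform accrual: 1 − [exp(−λ) − exp(−3.5λ)] / (2.5λ). This gives 0.0857 for λ = 0.04 and 0.0609 for λ = 0.028; mean 0.0733.
- Per group: 247 / (2 × 0.0733) ≈ 1,685, against 1,688 stated.

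The plan's figure reproduces from an unadjusted log-rank test. Section 6.7 plays no part in it.

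**2. Counting the baseline tests (SAP 8.1).**
- Continuous, clinical: 7 (age, height, weight, BMI, duration of morbidity, systolic and diastolic pressure).
- Continuous, laboratory: 13.
- Rows of Table 8.1, with age in two groupings: 22.
- Tests: 7 + 13 + 22 = 42.
- Repeats: age is tested three times, BMI and duration of morbidity twice each, so 2 + 1 + 1 = 4 repeats. Distinct variables: 42 − 4 = 38.
- Age, sex, subtype and mRS are already in the 9.1 item 4 model. Candidates that would add something new: 38 − 4 = 34.

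**3. Chance flags at 5% under sound randomisation.** Expected flags = k × 0.05; chance of at least one, if independent = 1 − 0.95^k.

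| k | Expected flags | At least one |
|---|---|---|
| 42 tests | 2.1 | 88.4% |
| 38 distinct variables | 1.9 | 85.8% |
| 34 outside the fixed model | 1.7 | 82.5% |

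**4. Correlation.** The documents give no correlations, so I assumed a common correlation among the 38 test statistics and simulated 100,000 trials for each value. The chance of at least one flag is about 84%, 80%, 73% and 56% for correlations of 0.1, 0.2, 0.3 and 0.5. The mean number of flags stays near 1.9.

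**5. The second condition.** Steps 3 and 4 cover significance only. How often a flagged difference would be judged medically important cannot be derived from the documents. As an illustration, if only 5 to 10 candidates could ever pass that judgement, the chance of at least one trigger under independence is 1 − 0.95⁵ = 23% to 1 − 0.95¹⁰ = 40%.

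**The case against.** The strongest reply is that little hangs on this. The confirmatory claim rests on the unadjusted log-rank test, with its significance levels set in SAP 6.5 and 6.6, and no decision attaches to any adjusted hazard ratio. SAP 9.1 lists only one adjusted model for the primary endpoint, so 6.7 can be read as a conditional sensitivity analysis, and the rule itself was written into the SAP finalised in March 2014. All of that stands, and it limits the point to a supportive estimate.

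Three stronger readings are tempting, and the documents support none of them:
- **That 6.7 is almost bound to fire.** The high percentages describe the first of two conditions. The medical judgement lowers them by an amount nobody can compute.
- **That the plan neglects prognostic factors that are balanced.** SAP 9.1 item 4 adjusts for four factors whatever their balance. The criticism applies only to how further factors are chosen.
- **That knowledge of allocation biases the choice.** The documents describe no blinding, and investigators learn the allocation (protocol 4.1), but nothing links that knowledge to covariate selection by the analysts. The gap is that 6.7 does not require blinding to outcome.

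It can also be said that not every difference need be chance. The first observation visit follows allocation by up to 30 days (protocol 6.2.1), and mRS and blood pressure are recorded then. Protocol 11.3 presents the baseline tests as a check for bias between groups. That is a fair reason to keep the tests as a check. It does not make significance a sound criterion for choosing covariates.

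**Conclusion.** The point holds for the supportive adjusted analysis. SAP 6.7 is a stated rule that selects covariates on imbalance and then on an undefined judgement, although an adjusted model is already fixed in both documents. Its significance step is more likely than not to flag something by chance: 82.5% for the 34 candidates outside the fixed model if independent, and 56% to 84% for all 38 variables over the correlations assumed. The 5% threshold is itself approximate under SAP 6.5. The count of 34 treats a flag on age, sex, subtype or mRS as adding nothing new; if the 6.7 model carried only the flagged factor, 38 would be the relevant count. The probability that both conditions are met is unknown.

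A reader might infer that the primary result or its type I error is at risk. It is not, because the log-rank test uses no covariates. The change is worth making but is not critical to the trial's main conclusion.

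**What to change.** Delete the significance trigger in SAP 6.7. State that the model in 9.1 item 4 (age, sex, clinical subtype, mRS) is the only pre-specified adjusted analysis of the primary endpoint. For any further adjusted model, either name its covariates in advance on prognostic grounds or label it exploratory.

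The baseline tests in SAP 8.1 may stay as a descriptive check, provided they do not drive covariate choice. Removing them would require aligning protocol 11.3, which calls for them. Adding factors to the item 4 model would also require alignment, because protocol 11.3 fixes the same four.

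The cost is SAP wording. Sample size, data collection and the primary test do not change. The downside is that an observed imbalance would no longer produce an adjusted model automatically; it could be examined only in an analysis labelled exploratory.

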## 6.8 Subgroup analysis

A subgroup analysis will be performed for the primary endpoint, using the variables shown in Table 6.8 as stratification variables. A Cox proportional hazard model for the primary endpoint that includes a comparison group and predictive factors will be examined. The hazard ratio for the combination therapy group versus the monotherapy group will be calculated for each stratification category based on the predictive factors. Uniformity will be examined for the stratification categories.

Table 6.8: Stratification Variables

| Item                                 | Category                                   |
|--------------------------------------|--------------------------------------------|
| Sex                                  | Male, Female                               |
| Age (yr)                             | up to 49, 50 to 59, 60 to 69, 70 and older |
|                                      | up to 64, 65 and older                     |
| BMI                                  | < 25, ≥ 25                                 |
| Past history and concomitant disease |                                            |
| Coronary artery disease              | No, Yes                                    |
| Peripheral artery disease            | No, Yes                                    |
| Hypertension                         | No, Yes                                    |

|                                                            |                           |
|------------------------------------------------------------|---------------------------|
| Diabetes mellitus                                          | No, Yes                   |
| Dyslipidemia                                               | No, Yes                   |
| Chronic renal disease                                      | No, Yes                   |
| History of symptomatic ischemic stroke                     | No, Yes                   |
| Habitual smoking                                           | No, Yes                   |
| Antiplatelet drugs *1                           | aspirin, clopidogrel      |
| Ischemic stroke clinical subtype                           | lacunar, atherothrombotic |
| At least 50% stenosis of an extracranial artery            | No, Yes                   |
| Degree of independence in activities of daily living (mRS) | 0, 1, 2, 3, 4, 5, 6       |

\* 1: At start of observations

## 6.9 Handling of patients with study drug administration errors

For all of the analyses, the data for these patients will be analyzed as data for the groups allocated to a treatment.

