### 11.2. Analysis populations

The intent-to-treat (ITT) analysis population used for evaluating safety and efficacy is defined as all randomly allocated study subjects. In compliance with the CONSORT Statement, we will create a flow diagram containing numbers of enrolled subjects, randomly allocated subjects, subjects observed for 1 year, subjects observed for 2 years, etc.

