#### **5. ANALYSIS SETS**

The efficacy and safety analyses will use the intent-to-treat (ITT) analysis set.

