##### **ITT analysis set**

The ITT analysis set is defined as the population of all randomized subjects. The subjects in this set belong to one of the treatment groups to which subjects were randomized, regardless of the drug they were actually administered.

The analysis set will be reexamined before database lock.

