## **10. SAFETY EVALUATION**

### **10.1 Adverse events**

Events that occur between the observation start date and the observation end date (during the observation period) will be included in the analysis. Adverse event summaries according to system organ class and type of event will be prepared using MedDRA/J.

- 1) The number of patients with adverse events and their incidence (100 x no. of patients with adverse events / no. of ITT patients) will be determined according to treatment group. The incidence of adverse events will be compared between groups using the chi-square test.
- 2) Incidence will be determined according to system organ class and event type (preferred term) based on terminology conversions using MedDRA/J, and the chi-square test will be used to compare these incidences across groups.
- 3) A frequency distribution for each level of severity will be determined based on the converted terms. If the same type of event occurs more than once in the same subject, the severest of these events will be used.

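### Adverse events and bleeding are analysed only by allocated arm over all randomised patients, with no supporting analysis by treatment actually taken

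*Supplement*

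**What the plan says.** Protocol v1.3 section 11.2 and SAP section 5 define one population for everything. The SAP states: "The efficacy and safety analyses will use the intent-to-treat (ITT) analysis set". It adds: "The ITT analysis set is defined as the population of all randomized subjects", and keeps each subject in the randomised group "regardless of the drug they were actually administered". SAP 6.9 repeats the rule for drug administration errors: "For all of the analyses, the data for these patients will be analyzed as data for the groups allocated to a treatment".

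SAP 10.1 gives adverse-event incidence as "100 x no. of patients with adverse events / no. of ITT patients", compared by chi-square. SAP 10.2 to 10.5 apply the same approach to adverse drug reactions, SAEs, serious adverse drug reactions and hemorrhage, including GUSTO severe or life-threatening hemorrhage, which is a named safety endpoint.

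The numerator is narrower than the denominator: "Events that occur between the observation start date and the observation end date (during the observation period) will be included in the analysis". Under protocol 6.2.1 observation starts at the first visit after allocation, up to 30 days after enrolment, and under protocol 5.1.2 cilostazol starts on that day.

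No treated set and no safety sensitivity analysis is defined. The only reservation is in SAP 5: "The analysis set will be reexamined before database lock". It names neither an alternative set nor a criterion.

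**The concern.** The study objective covers safety as well as efficacy, and the safety question is what adding cilostazol does to bleeding and serious events. Both arms already take aspirin or clopidogrel at entry, so only DAPT has a new drug to start. Three groups blur the comparison:

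- DAPT patients who are observed but never take cilostazol. They contribute SAPT-like risk to DAPT.
- SAPT patients who take cilostazol. Their bleeds are charged to SAPT.
- Patients in either arm who never reach the first observation day. They are counted below the line and cannot appear above it.

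For efficacy, the first two make a superiority claim harder to reach, which is conservative. For harm, they make an excess look smaller. Protocol 2 and 14.2 expect no added bleeding, so this dilution leans towards the expected finding, and no planned table shows how the comparison looks among patients who took the drug.

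**Working it through.** **The plan's own figure.** The documents give no expected bleeding rate and no safety power. The one computed figure is 1,688 per group for the log-rank test. With hazards 0.04 and 0.028 per year and follow-up uniform on 1 to 3.5 years, the event probability is 1 − (e^(−λ) − e^(−3.5λ))/(2.5λ), which gives 0.0857 and 0.0609 (mean 0.0733). Schoenfeld's formula needs 247 events, so 247/(2 × 0.0733) is about 1,686 per group. A Lakatos-type calculation gives 1,715. Both are within 3% of 1,688, so the sample size is not in question.

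**Inputs.** From the documents: 2,000 per arm, two-sided 5%. Assumed, because the documents are silent: all non-start and drop-in shares and all bleeding rates.

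**Part A: missed cilostazol and drop-in.** Let a be the share of DAPT patients who are observed without ever taking cilostazol, b the share of SAPT patients who take it, and RR the true risk ratio for cilostazol taken versus not taken. Then

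apparent RR = [RR(1 − a) + a] / [1 + (RR − 1)b].

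| a | b | True 1.5 appears as | True 2.0 appears as |
|---|---|---|---|
| 3% | 0 | 1.485 | 1.97 |
| 5% | 0 | 1.475 | 1.95 |
| 3% | 3% | 1.46 | 1.91 |
| 5% | 5% | 1.44 | 1.86 |
| 10% | 5% | 1.42 | 1.81 |

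Example for RR = 2, a = b = 5%: (2 × 0.95 + 0.05)/(1 + 0.05) = 1.95/1.05 = 1.86. In patients, with assumed risks of 1% and 2%, undiluted counts would be 20 and 40 per 2,000. DAPT becomes 2,000 × (0.95 × 0.02 + 0.05 × 0.01) = 39 and SAPT becomes 2,000 × (0.95 × 0.01 + 0.05 × 0.02) = 21.

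**Part B: never-observed patients.** Let f and g be the shares of DAPT and SAPT that never reach the first observation day. The table incidences are p1(1 − f) and p0(1 − g). With p0 = 1% and p1 = 2% assumed, and power for comparing two proportions at 2,000 per arm:

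| f (DAPT) | g (SAPT) | Difference, points | RR | Power |
|---|---|---|---|---|
| 0 | 0 | 1.00 | 2.00 | 74% |
| 5% | 5% | 0.95 | 2.00 | 72% |
| 5% | 1% | 0.91 | 1.92 | 67% |
| 10% | 2% | 0.82 | 1.84 | 60% |
| 1% | 5% | 1.03 | 2.08 | 77% |

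Equal shares cancel in the ratio, because (1 − f)/(1 − g) = 1, and shrink only the difference. Unequal shares move the ratio by (1 − f)/(1 − g), in either direction.

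**The case against.** Analysis by allocation is legitimate in an open comparison of two treatment strategies, and it preserves randomisation. That stands. The gap is only that it is the sole safety analysis.

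The exposure problem is also narrower than it first looks. Protocol 5.3 ends observation when study drug is stopped, so for patients who start, the event window is close to time on treatment. What remains is never-starters and wrong-drug patients. That stands too, and it is one reason the effect is modest.

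SAPT drop-in at 3% to 5% has no support in the documents. SAPT is defined as excluding cilostazol, and investigators know the allocation and confirm treatment status. This is why the results with b = 0 are shown separately; there, a risk ratio of 2.0 moves by only 1.5% to 2.5%.

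A reader might infer that the bias always runs towards no difference. The documents do not support this: it holds for Part A, but Part B can leave the ratio unchanged or inflate it.

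A reader might also infer that the harm comparison cannot be checked at all. That is too strong. SAP 7 reports discontinuation reasons by arm, SAP 8.2.1 compliance, and SAP 8.2.2 person-years. ICH or SAH is also analysed by log-rank and Cox under SAP 9.2.2, where never-observed patients add no time at risk. These show how much non-exposure there was. They do not show bleeding or SAEs by treatment taken, and the time-to-event analysis is still by allocated arm.

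Finally, the plan contains no formal test of no increase in bleeding, so there is no basis for requiring such a conclusion to hold in two sets.

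**Conclusion.** The gap is real and modest. Every planned adverse-event and bleeding table uses all randomised patients by allocated arm, and the promise to re-examine the set before lock does not say what would replace it or when. Missed cilostazol and drop-in pull the risk ratio towards 1. Never-observed patients reduce the absolute difference when their shares are equal, and can shift the ratio either way when they are not.

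The size rests entirely on assumed rates. For a true risk ratio of 2.0, the apparent value is 1.97 to 1.95 with 3% to 5% DAPT non-start alone, and 1.91 to 1.86 if the same share of SAPT takes cilostazol. This does not invalidate the ITT safety tables. It is a worthwhile low-cost addition, because safety is a stated objective and the needed data are already collected. It should be fixed in advance: sites know the allocation, so a set chosen shortly before lock would be open to influence from the results.

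**What to change.** Keep the ITT safety tables unchanged. In SAP 5, 6.9 and 10, add a supporting safety set: randomised patients who began observation and took at least one study drug, grouped by whether cilostazol was actually taken. Repeat three existing tables in it: GUSTO severe or life-threatening hemorrhage, all hemorrhagic events, and SAEs.

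Derive the grouping from the first-day drug records (protocol 6.3.1) together with the administration-status and other-drug records at later visits (6.3.2). First-day records alone are not enough: a prescription date does not show intake, and it misses cilostazol started later in SAPT. The definition should also say how a SAPT patient who starts cilostazol partway is counted, since events before that point did not occur on the drug.

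The cost is a few lines of SAP text and a second run of existing programs, with no new data or patients. The downside is that grouping by treatment taken is not fully randomised, so these tables support the ITT results and do not replace them.
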